### Outcomes and variables

The primary outcome of the trial is blood pressure control rate, which is the proportion of patients whose blood pressure is maintained within the target range. According to the National Basic Public Health Service Specification (Third Edition) [15], blood pressure should be controlled below 140/90 mmHg for individuals aged 35–65 years, and below 150/90 mmHg for those aged 65 years and above. Secondary outcomes: (1) standardized management rate: Calculated as the proportion of patients in the intervention and control groups who receive management in accordance with the National Basic Public Health Service Specification (Third Edition) [15], to evaluate the impact of the system on the standardization of hypertension management; (2) blood pressure measurement completion rate: The number of blood pressure measurements completed per patient compared to the expected quarterly measurements; (3) Referral rates: The number of patients referred to higher-level hospitals due to refractory or secondary hypertension, and the proportion of referred patients whose blood pressure stabilizes upon return; (4) Biochemical indicators: Changes in lipid profiles and other relevant biomarkers.

In addition, exploratory outcomes are economic evaluation(cost-effectiveness: analysis of system deployment costs versus improvements in hypertension control and reduced referrals; performance incentives: correlation between system-generated data and family doctor contract fulfillment metrics for incentive allocation), patient satisfaction (the subjective experiences and perceived effects), implementation barriers (engage professionals in focus groups and interviews to examine implementation barriers and improvement opportunities from the service providers’ perspective).

The satisfaction of patients in the control group is evaluated through a questionnaire survey with three questions:1. How satisfied are you with the overall hypertension management services currently provided by the community health service center? 2. How satisfied are you with the following aspects of the service? (a) Convenience of blood pressure monitoring. (b) Professional guidance from family doctors. (c) Timeliness of follow-up visits. A five-point Likert scale is used with the following response options: Very dissatisfied, somewhat dissatisfied, neutral, somewhat satisfied, very satisfied. 3. What aspects of the current hypertension management service do you think need the most improvement? (Open-ended question). Satisfaction in the intervention group is assessed using a dedicated questionnaire, with the specific design shown in Fig. 4.

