Patients in the intervention group can view their daily blood pressure conditions on the display. If there are any abnormalities, they can receive timely treatment. They can also print out the results, health education prescriptions, and blood pressure trend charts on-site. Managers can inquire about the number of people taking blood pressure measurements, the standardized management rate and the blood pressure control rate of each team in our hospital on a daily, monthly and quarterly basis. Once a month, the information is summarized, a team meeting is held to analyze the data collected by the system, statistics are analyzed and made public, the team is urged to strengthen the blood pressure management and strive to improve their own level, and the doctors are urged to refer patients affecting the control rate to the higher-level hospitals so as to form a good diagnosis and treatment pattern. The control group is managed in the traditional way. Patients only have their blood pressure measured in the health hut, and the data is not included in the new system for statistics. Management is carried out in accordance with the requirements of the “National Basic Public Health Service Specification (Third Edition) [15]”.

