### Study conduct

Eligible patients will be recruited via text messages or in-person during clinic appointments, explaining the study objectives, procedures, and voluntary nature of participation. Those interested will be contacted by research nurses for a telephone or in-person consultation to review the study details, including risks, benefits, and data confidentiality. Written informed consent will be obtained prior to enrollment. Upon consent, participants will complete a baseline assessment comprising: (1) demographics (age, sex, education); (2) clinical metrics: blood pressure (measured twice at rest, 5 min apart), BMI, fasting labs for lipids/glucose/renal/liver function, duration of hypertension, known comorbidities (e.g., diabetes, coronary artery disease); (3) functional assessment: mobility status (e.g., walking ability, use of assistive devices) and adherence to hypertension management (e.g., medication compliance, clinic visit frequency).

Following blood pressure measurement, the intervention group’s data will be automatically transmitted to the electronic health record system via IoT-enabled devices, where values are instantly integrated into statistical analyses and visualized on clinic display screens for real-time monitoring by both clinicians and patients. The system will trigger alerts for uncontrolled hypertension (systolic blood pressure is greater than 180 mmHg or diastolic blood pressure is greater than 110 mmHg [17]), enabling timely clinical decisions (medication adjustments/referrals). Participants will receive printed personalized reports with trend analyses and educational materials after each measurement. The control group will receive standard care via traditional health huts without IoT integration, with data manually recorded in electronic health records.

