A three-month interval is deemed adequate for the initial follow-up, given the service intensity and participants’ functional capacities. Both groups will undergo quarterly follow-ups (three months, six months, nine months, one year) to collect the primary outcome (blood pressure control rate) and secondary outcomes (standardized management rate, measurement completion rate, referral rates for refractory hypertension, changes in biochemical indicators like lipids and fasting glucose), with data collected from IG’s real-time IoT measurements and CG’s traditional health hut’s records. If participants do not proceed with subsequent follow-ups, they will be contacted by phone and encouraged to continue their involvement.

At the conclusion of the one-year trial, questionnaire surveys and interviews with professionals will be carried out. Professional interviews will be conducted via focus groups at the trial’s end. The discussions will be structured around three key themes: (1) System usage experiences: Exploring practical aspects of the IoT-based hypertension surveillance system, including its integration into clinical workflows, data accuracy, and any adaptations made during deployment. (2) Implementation challenges and facilitators: Identifying organizational factors (e.g., resource allocation), technical factors (e.g., device connectivity), and patient-related factors (e.g., adherence behaviors) that influence system effectiveness. (3) Program theory refinement: Examining how the intervention’s components (real-time monitoring, alerts, patient engagement tools) interact to achieve outcomes, and proposing improvements to optimize hypertension management pathways. Sessions will include physicians, nurses, and administrators to capture diverse perspectives. Additionally, assistance is provided throughout the study to help complete the survey, particularly for individuals with visual impairments or other difficulties.

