### Statistical analysis

Statistical analysis will be performed using SPSS 27.0. Normality of continuous variables (e.g., blood pressure values, biochemical indicators) will be assessed using Shapiro-Wilk tests. Normally distributed data will be presented as mean ± standard deviation (x̄ ± s) and analyzed with independent t-tests for between-group comparisons (intervention vs. control) and paired t-tests for within-group changes (baseline vs. follow-up). Non-normally distributed data will be reported as median (interquartile range) and analyzed using Mann-Whitney U test. Categorical variables will be expressed as counts (%) and compared via the chi-square test. A two-sided p-value < 0.05 will indicate statistical significance.

Intention-to-treat analysis will be prioritized [19], with multiple imputation for missing data. Subgroup analyses will be performed for age, hypertension severity, and comorbidity status. In addition, insights on implementation barriers and improvement strategies derived from focus groups and interviews with healthcare professionals will be systematically analyzed using thematic analysis.

The economic evaluation is integrated into the quasi-experimental trial design, comparing the IoT-based hypertension surveillance system (intervention group, IG) with standard care (control group, CG). Costs and outcomes are assessed over a 12-month period to determine incremental cost-effectiveness. The analytical method is Incremental Cost-Effectiveness Ratio (ICER) [20], which is calculated using the following method. Where: ΔC = Change in mean costs (intervention vs. control). ΔE = Change in mean effectiveness (e.g., blood pressure control rate). Bootstrap simulation with 1,000 replications will be conducted to generate ICER distributions, plotted graphically on cost-effectiveness planes.$$\:ICER=\frac{\left({\Delta\:}{C}_{IG}-{\Delta\:}{C}_{CG}\right)}{\left({\Delta\:}{E}_{IG}-{\Delta\:}{E}_{CG}\right)}$$

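### Stabilisation among referred patients compares two groups that the intervention itself helps to select, so the arms can differ on it with no effect on blood pressure

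*Protocol article*

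**What the plan says.** In the protocol article, Outcomes and variables, the third secondary outcome has two parts. The first is a count: "The number of patients referred to higher-level hospitals due to refractory or secondary hypertension". The second is a proportion: "the proportion of referred patients whose blood pressure stabilizes upon return".

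Two features of the intervention act on referral.
- Study intervention describes a monthly team meeting on the data the system has collected. The statistics are made public and "the doctors are urged to refer patients affecting the control rate to the higher-level hospitals".
- Study conduct describes alerts above 180 mmHg systolic or 110 mmHg diastolic, "enabling timely clinical decisions (medication adjustments/referrals").

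For the other arm, Study intervention says "The control group is managed in the traditional way", under the national public health service specification and outside the new system. Study conduct says "The control group will receive standard care via traditional health huts without IoT integration".

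The Objectives ask whether the intervention improves secondary outcomes, referral rates among them. Study conduct collects the secondary outcomes in both groups each quarter and there names "referral rates for refractory hypertension". Statistical analysis gives one general rule: "Categorical variables will be expressed as counts (%) and compared via the chi-square test", with significance at a two-sided p below 0.05.

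**The concern.** The denominator of the second part is not the enrolled group. It is the patients referred during follow-up, and referral is something the intervention sets out to change. If the two arms refer at different levels of severity, or for different reasons, the referred patients differ in how readily their blood pressure would settle, whatever the monitoring system does. Matching on age, sex and hypertension duration acts at baseline and cannot repair a selection made afterwards. Intention-to-treat keeps everyone in the assigned group but does not help when the analysis set is only those referred.

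At stake is a secondary result that could be reported as a benefit, or as a lack of one, and that reflects only case mix. The referral count has a related difficulty, because the sections do not agree on which reasons are counted.

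**Working it through.** **Is it a comparison between arms?** The protocol gives no separate test for this proportion. The Objectives treat secondary outcomes as effectiveness questions, Study conduct collects them in both groups, and the chi-square rule covers categorical variables without exception. Read together, these imply a chi-square test of stabilised/referred between arms.

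**Who enters the denominator?**

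| Route to referral | Intervention group | Control group |
|---|---|---|
| Usual care under the national specification | not excluded | yes |
| Monthly meeting urging referral | yes | none described |
| System alert feeding referral | yes | none described |

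The meeting works from the system's data. Control data are not in that system, so the push cannot reach control patients by the same route.

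**Which reasons are counted?** Objectives and Study conduct: refractory hypertension. Outcomes and variables: refractory or secondary hypertension. The meeting prompt is worded by effect on the team's control rate and matches neither.

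**Is there a figure to reproduce?** No. The protocol gives no expected referral share, stabilisation rate or power for this outcome. The two illustrations below use assumed inputs only. Both set the effect of the intervention on blood pressure to zero.

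*Illustration 1.* Severity s is standard normal in both arms. The most severe 5% of controls and 15% of intervention patients are referred, that is 50 and 150 of 1,000. The chance of stabilising is 1/(1 + exp(−(1.5 − b·s))) in both arms.

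| Slope b | Control | Intervention | Difference | Chi-square significant at 0.05 |
|---|---|---|---|---|
| 1.0 | 36.8% | 48.9% | 12.1 points | about 33% |
| 0.5 | 61.4% | 67.2% | 5.8 points | about 12% |

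*Illustration 2.* There are 1,000 patients per arm and 2,000 simulated trials. Systolic pressure has mean 141.5 mmHg, between-patient SD 12 and within-patient SD 8. Of patients at or above the referral level, 30% are referred. The intervention referral level is 140 mmHg and the control level varies. Stabilised means a return reading below 140 mmHg. The course after referral is the same in both arms.

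| Fall after referral | Control level | Mean referred (intervention / control) | Stabilised (intervention / control) | Significant |
|---|---|---|---|---|
| 0 | 140 | 163 / 162 | 23.5% / 23.5% | 5.4% |
| 0 | 150 | 162 / 83 | 23.6% / 11.9% | 61% |
| 0 | 160 | 163 / 30 | 23.6% / 4.2% | 77% |
| 10 mmHg | 140 | 162 / 163 | 54.8% / 54.8% | 4.2% |
| 10 mmHg | 150 | 163 / 83 | 54.6% / 38.3% | 68% |
| 10 mmHg | 160 | 162 / 30 | 54.8% / 21.1% | 94% |

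With the same referral level in both arms the test keeps its 5% level. With different levels it does not. The arms in this model differ only in referral level, so swapping the levels swaps the columns: if the intervention group were referred at the higher level, the same spurious difference would count against it.

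**The case against.** **No test is written for this proportion.** It appears once, as half of one secondary outcome, and descriptive reporting would be compatible with the text. That is true, but the general rule covers it and nothing exempts it, so a short clarification is warranted.

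**The count is limited to refractory or secondary hypertension.** If the denominator means that same set, milder patients referred only because they lower a team's control rate fall outside it, and selection through them does not operate. This stands as a limit on the mechanism. It does not remove the problem: the meeting and the alerts can also change how many patients with those diagnoses are found and referred, and the sections disagree on the reason set.

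**A reader might infer that intervention referrals must be milder, so that the bias favours the system.** The documents do not support that. The alerts above 180/110 mmHg draw in severe cases, and the balance between the two routes is unknown.

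**A reader might also infer that only intervention patients are referred under a rule.** That too goes beyond the text. Controls can be referred under usual care, and the referral provisions of the national specification are not shown. What is described for one arm only is the push and the alerts.

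**Part of a remedy is already in the plan.** Blood pressure control is the primary outcome, intention-to-treat is prioritised, and nothing removes referred patients from it. This is correct and limits what needs to change.

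**Conclusion.** The point holds in a bounded form. Stabilisation among referred patients has a denominator formed after baseline and shaped by the intervention. Neither matching nor intention-to-treat makes the two referred groups comparable, so a between-arm test of this proportion cannot be read as an effect on blood pressure.

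Neither the direction nor the size of the bias follows from the documents. The 6 to 12 point differences and the 12% to 94% rejection rates are illustrations and depend wholly on assumed referral shares, levels and slopes. In the milder illustration a spurious significant result is the less common outcome, at 12% to 33%. None of these figures should be quoted as the expected bias of this trial.

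The mismatch in counted reasons is a plain inconsistency, easily corrected. The primary outcome is not affected. The limitations in the Discussion concern non-random allocation and record quality. This selection is a separate matter and would remain even with perfect baseline matching.

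**What to change.** 1. In Outcomes and variables, state that stabilisation among referred patients is reported descriptively by arm, together with blood pressure at referral, without a between-arm test.
2. Define any tested referral comparison as a proportion of all enrolled patients in each arm. Read it as a process measure, since the intervention acts on referral directly.
3. Use one set of counted reasons in Objectives, Study conduct, and Outcomes and variables, and record the reason for every hypertension referral.
4. State that any claim of benefit rests on blood pressure control in all enrolled patients, which is already the primary outcome.

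The cost is a rewording of one secondary outcome, matching edits in two other sections and one field in the referral record. The downside is small: one tested secondary comparison becomes descriptive. No change to the clinical referral rules is proposed.

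### The economic evaluation credits fewer referrals while the intervention encourages referral, no direction is set for the referral outcome, and stabilisation is compared within a subset that the intervention itself selects

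*Protocol article*

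**What the plan says.** The Protocol article mentions referral in several places.

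- **Study intervention.** The system's data are reviewed monthly at a team meeting and made public, and "the doctors are urged to refer patients affecting the control rate to the higher-level hospitals". This is described for the intervention; control patients are managed in the traditional way.
- **Study conduct.** Alerts for very high readings in the intervention group are meant to help by "enabling timely clinical decisions (medication adjustments/referrals").
- **Objectives.** The second effectiveness question asks whether secondary outcomes improve, and names referral rates for refractory hypertension among them. It does not say whether improvement means more or fewer.
- **Outcomes and variables, secondary outcome 3.** This is the number of patients referred for refractory or secondary hypertension, together with "the proportion of referred patients whose blood pressure stabilizes upon return". No direction is given here either.
- **Outcomes and variables, exploratory outcomes.** Cost-effectiveness is "analysis of system deployment costs versus improvements in hypertension control and reduced referrals".
- **Statistical analysis.** The effect term of the cost-effectiveness ratio is "ΔE = Change in mean effectiveness (e.g., blood pressure control rate"). Referrals are not named there. The Abstract says that costs come from administrative data on healthcare use and from intervention costs.

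The primary outcome is "the proportion of patients whose blood pressure is maintained within the target range". Follow-up data are gathered quarterly, "with data collected from IG’s real-time IoT measurements and CG’s traditional health hut’s records". On the analysis set, the article says: "Intention-to-treat analysis will be prioritized [19], with multiple imputation for missing data".

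**The concern.** The intervention pushes referral up for patients who lower a team's control rate, while the economic outcome treats a fall in referrals as a gain. If the system works as designed, its own action is scored against it. If referrals fall, that can be called a saving, or it can be called a failure to act on the monthly review. With no direction fixed for the secondary outcome, either result could be presented as success once the data are seen.

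The second issue is the stabilisation proportion. Its denominator is formed after baseline by a decision that one arm is encouraged to take more often. A difference between arms may then reflect who was referred and not how well they did.

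The third issue is a possibility only. Referral is aimed at patients defined by the primary outcome, and intervention readings come from on-site devices. If referral led to missing readings for uncontrolled patients, the control rate could be affected.

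**Working it through.** **1. Direction of referral.** The document gives no referral rate or target, so there is no figure to reproduce. The statements compare as follows.

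| Place | Role of referral | Direction |
|---|---|---|
| Study intervention | action urged at monthly review | up, for patients who lower the control rate |
| Study conduct | possible response to an alert | up, or neutral |
| Objectives | secondary outcome that may improve | not stated |
| Outcomes and variables, secondary | count of referred patients | not stated |
| Outcomes and variables, exploratory | benefit set against deployment cost | down |

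The first and last rows pull in opposite directions, and no text links them, for example by expecting an early rise and a later fall.

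**2. Counting in the economic evaluation.** Referral care is healthcare use, so it fits the cost term that the Abstract describes. If it is in the cost term and fewer referrals are also credited as a separate benefit, the same event counts twice.

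**3. Stabilisation among the referred.** Suppose referred patients are of two kinds: harder cases, who stabilise with probability s1, and milder cases, who stabilise with a higher probability s2. If a share w of an arm's referrals are harder cases, the reported proportion is

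w × s1 + (1 − w) × s2.

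Let s1 and s2 be equal in the two arms. If wider referral in the intervention arm brings in more of the milder cases, its w is smaller and its proportion is higher, with no difference in outcome for any given type of patient. If wider referral adds harder cases, the sign reverses. Baseline matching on age, sex and hypertension duration applies to the enrolled groups and does not carry over to the referred subsets.

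**4. Primary outcome: size of the risk.** From the Sample size calculation section: control rate 45%, planned intervention rate 55%, 1,000 patients per arm. The following are assumptions: true control is 45% in both arms (450 controlled, 550 uncontrolled); every lost patient was referred, uncontrolled and never measured again; loss occurs in the intervention arm only; and lost patients are dropped from the denominator.

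Apparent rate = 450 / (1,000 − number lost).

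| Lost | Share of arm | Share of the 550 uncontrolled | Apparent rate | Shift |
|---|---|---|---|---|
| 27.5 | 2.75% | 5% | 450/972.5 = 46.3% | +1.3 points |
| 50 | 5% | 9.1% | 450/950 = 47.4% | +2.4 points |
| 55 | 5.5% | 10% | 450/945 = 47.6% | +2.6 points |
| 100 | 10% | 18.2% | 450/900 = 50.0% | +5.0 points |
| 110 | 11% | 20% | 450/890 = 50.6% | +5.6 points |

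With no true effect, the chance of a significant result would be about 8%, 21% and 68% for 5%, 10% and 20% of the uncontrolled patients lost, against a nominal 5%.

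These are upper bounds for each assumed loss, because they are complete-case results. If all referred patients are measured, the shift is 450/1,000 − 45% = 0. If the control arm loses the same share of uncontrolled patients, the difference between arms is also zero.

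**The case against.** **The statements are not a strict contradiction.** A reader might infer that they cannot both be true. That is too strong: one describes an action at a monthly meeting and the other a result hoped for over a year, and referrals could rise for resistant cases and fall later as control improves. This stands. However, the document does not say so, and the tension remains.

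**The economic effect is limited.** The credit for fewer referrals is one phrase under the exploratory outcomes. The ratio itself gives the control rate as its example of effect, and entering referrals as resource use may already be intended. Moving referrals into cost also means that extra referral still weighs against the system. All of this is fair. The change removes the double credit and leaves a real resource use to be weighed against any gain in control.

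**The stabilisation figure may be only a descriptor of the referral pathway.** That use is harmless, but the figure is listed within a secondary outcome collected in both arms, so a comparison is likely.

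**The primary outcome.** A reader might infer that referral removes uncontrolled patients and inflates the control rate. The documents do not support this. Nothing takes referred patients out of the denominator, intention-to-treat with multiple imputation is prioritised, quarterly follow-up includes telephone contact for those who stop attending, and referred patients are expected to return. An imputation model using earlier readings would pull such patients towards uncontrolled. That model may be specified in an analysis plan that is not shown, so its absence here is no fault.

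**Conclusion.** The concern holds for the referral outcome. The article encourages referral as part of the intervention, credits its reduction in the economic evaluation, and sets no direction for it as a secondary outcome. This is a tension that needs reconciling and falls short of a logical impossibility. It reaches one secondary and one exploratory outcome. The comparison of stabilisation among referred patients is not interpretable as an effect of the system, because the intervention influences who is in the denominator.

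For the primary outcome there is only a risk. Its size depends wholly on an assumed loss that the documents do not give: from zero, if referred patients are measured, up to 2.4 points if 5% of the intervention arm is lost or 5.0 points if 10% is lost. Both figures require that everyone lost was uncontrolled, that no such loss occurs in the control arm, and that lost patients are dropped and not imputed. No view is taken here on which referral practice is right.

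**What to change.** 1. Reconcile Objectives, Study intervention and Outcomes and variables. State in advance what role the referral outcome has: a named direction, or a neutral process measure. This need not prescribe any referral practice.
2. In the economic evaluation, count referrals once, as resource use in the cost term, and remove fewer referrals as a separate benefit.
3. Report the numbers referred, and the numbers referred and stabilised, per arm over all enrolled patients. Give the proportion among referred patients as description only. The count over all enrolled patients still depends on how many are referred, so show the two counts together.
4. As a safeguard, state that referred patients stay in the denominator of the control rate. Add one sensitivity analysis that counts referred patients without a 12-month reading as not controlled. Under the assumptions in the working this returns 450/1,000 = 45.0%. It is deliberately strict, since some of those patients may in fact be controlled.

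The cost is some rewording and one extra analysis. The sensitivity estimate may be somewhat less favourable to the system. The sample size and data collection do not change.
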